**Figure 4 F4:**
[figure not shown]
Using interrupted time series analysis to measure change before and after intervention. Adapted from Kontopantelis et al 2015 [13].

Regarding patient and family reported outcomes, we will describe them at each survey time point using mean and standard deviation, or median and inter-quartile range. We will conduct regression analysis of these outcomes at each survey (pre-intervention, 6-month and 12-month post-intervention), respectively, with intervention status as the main independent variable. We will control for participants’ socio-demographic, clinical and baseline outcome variables, and use the GEE approach to account for potential clustering effect by site. We will conduct intention-to-treat analysis.

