**Figure 1 F1:**
[figure not shown]
Local Health Districts involved in the RuralKidsGPS study.

The primary aim of this evaluation is to assess the impact of RuralKidsGPS on health service utilisation (ED presentations, hospital admissions, and outpatient (OP) appointments), among CYP enrolled in RuralKidsGPS intervention compared to usual care.

The secondary aims are to:

Describe trends in health service utilisation (ED presentations, hospital admissions, OP appointments, and general practice (GP) attendances) over time;Assess the change in parent reported satisfaction with care, parental wellbeing, and parent and CYP reported quality of life at enrolment, at 6 and 12 months after recruitment to RuralKidsGPS;Assess the implementation of RuralKidsGPS model from the perspective of families, CYP, healthcare providers, managers, and practitioners, and factors that help or hinder this implementation to inform further adaption of the model and ensure scalability;Assess the cost-effectiveness of RuralKidsGPS model of care compared with standard care.

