### Impact evaluation

#### Health Service Use

A cohort-level evaluation of health utilisation (primary outcome) will be conducted. A cohort of children receiving the RuralKidsGPS will be recruited from the participating LHDs. Routinely collected administrative health data for these children will be requested and linked by an independent group, the NSW Centre for Health Record Linkage (CHeReL) (Figure 3). Using this deidentified linked data, we will compare the change and trend in health utilisation of children (ED presentations, hospital admissions, and outpatient (OP) appointments) who received RuralKidsGPS, to that of a matched comparison group.

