**Figure 3 F3:**
[figure not shown]
Sources of data for linkage.

The comparison group will be identified using the linked administrative health data (ED presentations, hospital admissions, and OP appointments) and frequency matched with 20 children (to each case) by clinical diagnosis, year of birth, sex, local health district who and meet the eligibility criteria for health service use within the past 6 months (outlined in the Study Cohort section above) but who did not access RuralKidsGPS. A population-level evaluation will also be conducted which will include all CYP in the 4 health districts meeting the inclusion criteria.

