#### Impact Evaluation: Patient and family reported outcomes data collection

In our intervention cohort, secondary child and parent reported outcomes will assess family reported experiences and parental satisfaction with care integration (PICS) [6], out of pocket expenses (adapted Mumford Scale) [7], parent and child quality of life (EQ5D5L) [8], (PedsQL4.0) [9], (CHU9D) [10] and parental wellbeing (WEMWBS) [11]. These measures and basic demographic data (e.g. date of birth, postcode for estimation of Indexes of Relative Advantage and Disadvantage [12], gender, Aboriginal and Torres Strait Islander Status) will be collected via phone and secure electronic survey by a researcher embedded in each of the LHDs, at three time points: enrolment, 6 months and 12 months later to enable longitudinal comparisons, (Table 1).

**Table 1 T1:** Family reported outcome measures.

OUTCOME MEASURES	PURPOSE

Paediatric Integrated Care Survey (PICS) [6]	Measures experiences of integration of child’s care

Adapted Mumford scale [7]	Measuring non-medical out of pocket expenses for families

EuroQol 5 Dimension 5 Level (EQ-5D-5L) [8]	Health status measure

Paediatric Quality of Life Measure (PedsQL4.0) [9]	Measuring health paediatric health outcomes

Child Health Utility 9D (CHU 9D) [10]	Instrument used to adjust quality of life years from PedsQL4.0 score for economic evaluation

Warwick-Edinburgh Mental Well-being Scale (WEMWBS) [11]	Understanding and measuring mental health and wellbeing

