#### Implementation evaluation analyses

All instruments will be scored according to the manuals provided by the authors who initially developed these tools. Measures will be compared over time using t-tests for simple comparisons, or analysis of variance (ANOVA) for comparisons across three time points based on available data (see Table 3). The Routinization and Sustainability of work practices in long term care tool [18] will be used only after RuralKidsGPS has been operational for at least 12 months, providing a one-time measure. This may be repeated in the future if it is decided that the model of care will continue to be supported beyond the current study period.

The three-step iterative process for coding the interview and focus group data will be used to ensure intercoder reliability [19]. The initial stage will involve researchers using the CFIR to independently code an interview transcript. This coding along with inductive insights identified in transcripts will be compared for reliability among the research team and any inconsistencies will be discussed and agreed upon. This process has been shown to lead to a high degree of intercoder reliability among the research team [20]. Once intercoder reliability is established, the remainder of the transcripts will be coded. We will be guided by the Consolidated criteria for Reporting Qualitative research (COREQ) checklist for qualitative research [21]. Qualitative and quantitative data will be synthesised through holistic triangulation [22] to arrive at a deep understanding of the data to answer the questions posed in Table 4.

**Table 4 T4:** Sources, measures, and tools for evaluation.

RESEARCH QUESTION	DATA SOURCE

*1. What is the impact of RuralKidsGPS on health service use?*	Linked data from multiple sources Figure 3

*2. What is the impact of RuralKidsGPS on family reported experiences, and parental satisfaction with care and care coordination?*	Paediatric Integrated Care Survey [6]

*3. What is the family impact related to the child’s healthcare needs (travel and accommodation costs, care for siblings, missed work, missed school days)?*	Adapted Mumford Survey [7].

*4. What is the impact of RuralKidsGPS on parent and child related Quality of Life?*	Parents: EQ-5D-5L [8] Children aged <7 years: Parent reported Paediatric Quality of Life Inventory [9] CYP aged 7–17 years: CHU9D [10]

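### Family-reported outcomes are collected only from intervention families, so the planned regression on intervention status has no contrast and cannot be estimated

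*Protocol article*

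**What the plan says.** **Who is surveyed.** The section on patient and family reported outcomes data collection opens: "In our intervention cohort, secondary child and parent reported outcomes will assess family reported experiences". It goes on to list all six instruments, collected "at three time points: enrolment, 6 months and 12 months later to enable longitudinal comparisons". The Recruitment section gives one route for families: the child is enrolled in the local service, the care coordinator raises the evaluation, and the embedded researcher then makes contact.

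**Where the comparison group comes from.** Below Figure 3: "The comparison group will be identified using the linked administrative health data (ED presentations, hospital admissions, and OP appointments" and so on. The Health Service Use section describes the dataset and its purpose: "Using this deidentified linked data, we will compare the change and trend in health utilisation of children". No approach to comparison families, consent or questionnaire is described.

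**What the aim is.** The secondary aim under Study design is to "Assess the change in parent reported satisfaction with care, parental wellbeing, and parent and CYP reported quality of life at enrolment" and at 6 and 12 months after recruitment to the service.

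**What the analysis is.** The last paragraph of Impact Evaluation Analyses (below Figure 4) plans descriptive summaries at each survey, then a "regression analysis of these outcomes at each survey (pre-intervention, 6-month and 12-month post-intervention), respectively, with intervention status as the main independent variable". The next sentence adds adjustment for socio-demographic, clinical and baseline outcome variables. Earlier in the same section, in the utilisation model, intervention status is defined as intervention versus comparison.

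**The concern.** Data collection and analysis contradict each other. The regression needs two groups of survey respondents, and the data collection produces one. Both statements are affirmative, so this is not detail that a condensed article leaves to an analysis plan. A later plan could add detail, but it could not supply comparison questionnaires that are not collected. It would have to replace the sentence.

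Two things are at stake. First, the only inferential model in the impact evaluation for these outcomes cannot be run, so its replacement would be chosen after the data are in hand. Second, Table 4 asks in questions 2, 4 and 5 about the impact of the programme on family experience, quality of life and parental wellbeing. The methods describe a controlled comparison, whereas the data can give only uncontrolled change. Children aged 6 months or more enter because of frequent recent service use (Study cohort), so part of any change after enrolment may be regression to the mean. A reader should not take it for an effect against usual care.

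**Working it through.** **Step 1. Is the status coefficient estimable at one survey?** Inputs: respondents are the intervention cohort only (data collection section); status means intervention versus comparison (Impact Evaluation Analyses); target of 400 children (same section).

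- Status = 1 for all respondents, so its variance is 0 and its column equals the intercept column.
- A design with intercept, status and two illustrative covariates for 400 respondents has 4 columns and rank 3. The status coefficient is not identified. This does not depend on the sample size or on any assumed parameter.

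**Step 2. Does another reading rescue it?**

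- Status read as before/after: the models are fitted separately at each survey, and within one survey every family has the same before/after value. The column is again constant.
- Three surveys stacked, with status added to intercept and two time indicators: 4 columns, rank 3. It fails again.
- The same stacked design without status: 3 columns, rank 3. Change at 6 and at 12 months is estimable.

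**Step 3. Does the regression answer the stated aim?** The aim is change after enrolment. None of the three separate models contains time, so none has a coefficient for change. At the pre-intervention survey, adjustment for the baseline outcome puts the same value on both sides of the equation.

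**Step 4. The plan's own figure for these outcomes.** Impact Evaluation Analyses says that the sample also allows detection of a 4.36-point change in the PedsQL total score from before to after the intervention. No SD is given, so the claim cannot be reproduced, only bounded. Assumptions that are mine: two-sided 5%, normal approximation for paired data, and the SDs of change shown below.

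- Largest tolerable SD of change = 4.36 × √n / (z for alpha + z for power).
- n = 400, 90% power: 4.36 × 20 / (1.960 + 1.282) = 26.9. At 80% power: 4.36 × 20 / (1.960 + 0.842) = 31.1.
- n = 200, 90% power: 19.0.

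Power for 4.36 points with 400 complete pairs:

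| SD of change (assumed) | Power |
|---|---|
| 15 | above 99.9% |
| 20 | 99.2% |
| 25 | 93.7% |
| 30 | 82.8% |

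The sizing statement is plausible, but it supports a before-and-after analysis and not a comparison by status. It also presumes that all 400 children contribute PedsQL pairs. Table 4 lists PedsQL for children under 7 and CHU9D for ages 7 to 17, so the number of pairs may be smaller.

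**The case against.** The strongest reply is that this is one misplaced sentence and not a failed objective. The secondary aim claims no comparison with usual care, and the PedsQL sizing is already a before-and-after statement. That is fair. It limits the point to the regression on status and to the impact wording in Table 4. It does not make the regression estimable.

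Four stronger readings are tempting, and the document does not support them.

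- A reader might infer that no family-reported outcome can be analysed at all. Means with SDs, or medians with quartile ranges, are planned at each survey. The implementation section also says: "Measures will be compared over time using t-tests for simple comparisons, or analysis of variance (ANOVA) for comparisons across three time points", and Table 3 schedules PICS for families at all three times. These remain feasible.
- A reader might infer that those t-tests and ANOVA ignore repeated measurement. The article does not say that they are unpaired, and comparing over time is consistent with paired tests and repeated-measures ANOVA. That detail can sit in an analysis plan.
- A reader might infer that PICS has two conflicting analyses. It serves two components, impact and implementation. Using it in both is not a contradiction in itself.
- A reader might extend the remedy to the staff surveys. One staff tool is a one-time measure, another is given only twice, and the article does not say that staff responses are linked across waves. The remedy is therefore confined to the family-reported outcomes.

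The baseline-covariate defect is minor. It could be read as meant for the 6- and 12-month surveys only, although the text does not exempt the pre-intervention survey. It disappears once the main sentence is replaced.

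**Conclusion.** The point holds as stated. With 0 comparison families surveyed, the planned coefficient for intervention status is not estimable at any of the three surveys, and the model has no term for the within-family change that the aim names. This is structural. It rests only on the article's statements of who is surveyed and what intervention status means, and nothing elsewhere in the article supplies comparison survey data. The SDs assumed above bear only on the PedsQL sizing and not on this conclusion.

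The defect is confined to the regression for the secondary family-reported outcomes and to the impact wording attached to them. The primary utilisation comparison uses linked data for both groups, and the economic formulas are already before-and-after, so neither uses this regression. It still needs correcting before analysis, because the sentence as written cannot be carried out.

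**What to change.** Replace the regression sentence in the last paragraph of Impact Evaluation Analyses with one longitudinal model per family-reported outcome:

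- All three surveys in one model, with time (0, 6, 12 months) as the main factor.
- Within-family correlation accounted for, for example by a random intercept per family.
- Site accounted for, and the planned socio-demographic and clinical covariates kept. The enrolment value becomes the time-0 outcome and is no longer a covariate.
- Mean change at 6 and at 12 months reported with confidence intervals.
- A statement that these are uncontrolled within-family changes and not effects against usual care.

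Reword questions 2, 4 and 5 of Table 4 to ask about change after enrolment. The cost is protocol and analysis plan wording only, with no new data.

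The alternative that would keep the status regression at the 6- and 12-month surveys is to recruit and survey a concurrent comparison group. For 4.36 PedsQL points at 90% power that needs n per group = 2 × (SD × 3.242 / 4.36)², which is 249, 443 or 691 per group at assumed SDs of 15, 20 or 25. That means new recruitment and consent, and the stated aim does not require it.

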### Implementation Evaluation

We will undertake a mixed methods implementation evaluation, underpinned by the Consolidated Framework for Implementation Research (CFIR) [14]. The CFIR is a comprehensive meta-theoretical framework that provides a taxonomy of standardised operationally defined constructs to guide systematic assessment in the identification of factors (barriers and enablers) influencing implementation of complex programs within complex contexts [14]. Contextually relevant strategies for successful implementation as well as barriers and facilitators for adoption, delivery and sustainability will be identified to inform future rollouts of the RuralKidsGPS model of care. The mixed methods research will also assess implementation outcomes including acceptability, appropriateness, and adaptability of the RuralKidsGPS model as viewed by children and families, healthcare providers, and service managers, informing answers to specific questions that reflect implementation outcomes proposed by Proctor et al., (2011) (Table 2) [15].

**Table 2 T2:** Defining implementation outcomes for RuralKidsGPS, based on Proctor’s framework.

OUTCOME	QUESTION

Acceptability	Do clinician and non-clinicians, parents and children view RuralKidsGPS as agreeable?

Adoption	To what extent do clinicians and parents use RuralKidsGPS?

Appropriateness	Do all stakeholders perceive RuralKidsGPS as relevant & useful?

Fidelity	Is RuralKidsGPS applied as intended? Are all component parts of the intervention delivered as planned?

Feasibility	Are the component parts of RuralKidsGPS practical to deliver within the service?

Coverage	How many service users of those eligible are reached?

Cost*	How much does it cost to successfully implement RuralKidsGPS?

Sustainability	What are the factors that will allow RuralKidsGPS to be scaled-up further?

*This outcome will be informed by the economic evaluation.

#### Implementation evaluation qualitative data collection

Semi-structured interviews will be undertaken by trained researchers with CYP aged over seven years, their parents, or caregivers, after they have been accessing RuralKidsGPS for at least 6 months. Children aged over seven years are considered capable of understanding the purpose of the research and of making informed decisions as to whether to participate in a brief interview or not [16].

Healthcare providers and managers involved in delivering the model of care will also be interviewed between 6 and 12 months after implementation of RuralKidsGPS. Purposive sampling will be used to recruit a diverse sample of service users (children, young people, and families) and providers across the four sites. Key stakeholder workshops held within each LHD, will present findings to enable reflection on the appropriateness and acceptability of the model, identify future adjustments to the model and implementation strategies with consideration of local contexts. The outcomes of the workshops will inform the development of an implementation guide to support future scaling up of RuralKidsGPS.

#### Implementation evaluation quantitative data collection

Data will be collected for each child before and after enrolment in the RuralKidsGPS care coordination model. In addition, key LHD staff involved in the delivery or management of RuralKidsGPS will be sent a link to a secure online survey, which includes the Acceptability, Appropriateness and Feasibility measure [15], Normalization Process Theory (NoMAD) tool [17] and Routinisation and Sustainability of work practices in long term care [18], at three time points: enrolment, 6 months and 12 months later as described in Table 3.

**Table 3 T3:** Quantitative data collection for children and families, clinician and non-clinicians at each of the four sites.

GROUP	INSTRUMENT	BASELINE (ENROLMENT)	6 MONTHS	12 MONTHS

Families	Paediatric Integrated Care Survey [6]	x	x	x

Clinician and non-clinicians	Intervention Acceptability, Appropriateness and Feasibility measure [15]	x	x	x

Clinicians and non-clinicians	NoMAD (Normalization Process Theory tool) [17]		x	x

Clinician and non-clinicians	Routinisation and sustainability of work practices in long term care [18]			x

#### Implementation evaluation analyses

All instruments will be scored according to the manuals provided by the authors who initially developed these tools. Measures will be compared over time using t-tests for simple comparisons, or analysis of variance (ANOVA) for comparisons across three time points based on available data (see Table 3). The Routinization and Sustainability of work practices in long term care tool [18] will be used only after RuralKidsGPS has been operational for at least 12 months, providing a one-time measure. This may be repeated in the future if it is decided that the model of care will continue to be supported beyond the current study period.

The three-step iterative process for coding the interview and focus group data will be used to ensure intercoder reliability [19]. The initial stage will involve researchers using the CFIR to independently code an interview transcript. This coding along with inductive insights identified in transcripts will be compared for reliability among the research team and any inconsistencies will be discussed and agreed upon. This process has been shown to lead to a high degree of intercoder reliability among the research team [20]. Once intercoder reliability is established, the remainder of the transcripts will be coded. We will be guided by the Consolidated criteria for Reporting Qualitative research (COREQ) checklist for qualitative research [21]. Qualitative and quantitative data will be synthesised through holistic triangulation [22] to arrive at a deep understanding of the data to answer the questions posed in Table 4.

**Table 4 T4:** Sources, measures, and tools for evaluation.

RESEARCH QUESTION	DATA SOURCE

*1. What is the impact of RuralKidsGPS on health service use?*	Linked data from multiple sources Figure 3

*2. What is the impact of RuralKidsGPS on family reported experiences, and parental satisfaction with care and care coordination?*	Paediatric Integrated Care Survey [6]

*3. What is the family impact related to the child’s healthcare needs (travel and accommodation costs, care for siblings, missed work, missed school days)?*	Adapted Mumford Survey [7].

*4. What is the impact of RuralKidsGPS on parent and child related Quality of Life?*	Parents: EQ-5D-5L [8] Children aged <7 years: Parent reported Paediatric Quality of Life Inventory [9] CYP aged 7–17 years: CHU9D [10]

*5. What is the impact of RuralKidsGPS on Parental mental wellbeing?*	Warwick-Edinburgh Mental Well-being scale [11]

*6. What is the cost of implementing the model of care? What is the cost effectiveness?*	Average costs per encounter in health service use (ED presentation, hospital admission, outpatients encounter); family cost estimates according to adapted method of Mumford et al., 2018 [7]; Quality adjusted life-years (QALYs)

*7. What are the aspects of the model of care and its implementation that support feasibility, acceptability and contextual appropriateness?*	Qualitative semi-structured interviews guided by the Consolidated Framework for Implementation Research [25]; and the Proctor Implementation Outcomes Framework [15].

*8. What are the barriers and enablers for implementing the model at scale?*	Qualitative semi-structured interviews guided by the Consolidated Framework for Implementation Research [25]; and the Proctor Implementation Outcomes Framework [15].

*9. What are the factors that will allow RuralKidsGPS to be scaled-up further?*	Survey for healthcare professionals, researchers and health care managers that includes validated tools: Short intervention acceptability, appropriateness, and feasibility measure [15], Normalization Process Theory Nomad Tool [17], Routinisation and sustainability of work practices in long term care [18].

Using NVivo qualitative data analysis software [23] we will undertake thematic analysis taking a hybrid inductive/deductive approach [24] to identify factors that help or hinder implementation, and these factors will be categorised under the CFIR constructs. Thematic analysis will specifically focus on barriers and enablers of effective behaviour change in terms of engagement with services and operation of the new model of care, whilst taking local site contextual factors into account. Such factors may include details of the setting, resource availability, staff attitudes, capabilities and capacity, and level of support from management.

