### Study cohort

The study population includes CYP with medical complexity aged 0 to 18 years, referred for care coordination, who meet the following criteria:

– A diagnosis expected to last at least 12 months– And if ≥ 6months of age, frequent use of health services within the last six-month period, defined as:Two or more ED presentations, ORHospital admission for seven days or more, ORTwo or more outpatient appointments.

A cohort of CYP meeting these criteria and referred for care coordination, their parents and guardians, and clinical and non-clinical staff involved in the planning and/or delivery of the RuralKidsGPS model of care, will all form a part of the study cohort.

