#### Impact Evaluation Analyses

Based on local data from the participating LHDs, we aim to recruit 400 children across the four LHDs. We will match each case by 20 controls, resulting in a total of 8,000 controls. This will provide 90% power to detect a 20% difference in the number of health service use occasions, including outpatient visits and hospital admissions between intervention and comparison groups. Having 400 cases will also provide the power of 90% to detect a within-group 20% decrease in the number of health service use occasions. This sample size will also allow us to detect a clinically important difference (4.36 points) for child health related quality of life in children post- vs pre-intervention change in the PedsQL4.0 Total Scale Score [9].

We will calculate rate of health service use (e.g. ED, hospital admissions and OP visits) in person-years for the intervention and comparison groups during the baseline (3 years prior to enrolment) and the intervention period (12 months after enrolment), respectively. To assess the effectiveness of this intervention, we will conduct multivariable Poisson (negative binomial if over-dispersion is present) regression analysis with intervention status (intervention versus comparison) as the main independent variable and the rate of health service use (ED, hospital admissions and OP visits, separately and combined) during the intervention period as the outcome variable.

To examine how health service use changes over time between intervention and comparison groups, we will analyse rates of health service use during baseline and intervention periods using mixed effect Poisson regression models, including the interaction term between intervention status and time (after RuralKidsGPS implementation versus before RuralKidsGPS). In all regression analyses, we will control for participant socio-demographics (e.g., age at enrolment, sex, Aboriginal and Torres Strait Islander status, socio-economic status) and clinical factors (e.g., type and severity of health conditions), and baseline rate of health service use. Considering potential clustering effect by site, we will use the generalised estimating equations (GEE) approach in the regression analysis.

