Outcome data will capture changes to parent and child reported quality of life assessed using the validated instruments EQ5D5L15 (parent) [8] and Paediatric Quality of Life Inventory (PedsQL4.0), and Child Health Utility 9D (CHU9D) [10] (internal consistency 𝛼 = 0.89 children and 0.92 parent report). These utilities will be included in the estimation of QALYs (quality-adjusted life-years) by calculating the area under the curve, assuming a linear change between the survey dates. QALYs calculated for the year before the intervention starts are based on the health state utility measured at baseline, which was assumed to be stable during the year before.

Cost-effectiveness will be expressed as incremental change in costs (measured by ED presentations, hospital admissions, or OP visits averted), and cost-utility by changes in QALYs gained. Cost-effectiveness will be measured between pre and post implementation of the intervention and calculated according to the formulas below:

\[\begin{array}{l}
Effect\ differences:\ \Delta QALYs = QALY{s_{post\ new\ model\ of\ care}} - QALY{s_{pre\ new\ model\ of\ care}}
\end{array}\]

\[\begin{array}{l}
Cost\ differences:\ \Delta Total\ costs = Total\ cost{s_{postnew\ model\ of\ care}} - Total\ cost{s_{pre\ new\ model\ of\ care}}
\end{array}\]

Imputation methods will be applied to missing values and sensitivity analyses will be conducted for key cost parameters in the data sets to ensure the robustness of the estimates. An additional bootstrap analysis with random 1,000-fold resampling of the original population will be conducted to ensure the validity of confidence intervals.

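### The PedsQL detectability claim rests on 400 children aged 0 to 18, but Table 4 gives PedsQL only to under-7s and CHU9D only to ages 7–17; the sections must be reconciled

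*Protocol article*

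**What the plan says.** The Study cohort section sets the age range: "The study population includes CYP with medical complexity aged 0 to 18 years". Impact Evaluation Analyses gives the target, "we aim to recruit 400 children across the four LHDs", and adds a claim on child quality of life: "This sample size will also allow us to detect a clinically important difference (4.36 points", specified as the "post- vs pre-intervention change in the PedsQL4.0 Total Scale Score". It attaches no age restriction to that claim, and no SD, significance level or power. The 90% power in the same paragraph refers to health service use.

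The section on patient and family reported outcomes lists EQ-5D-5L, PedsQL and CHU9D for the intervention cohort at enrolment, 6 and 12 months, again without an age split. Its Table 1 describes CHU9D as "Instrument used to adjust quality of life years from PedsQL4.0 score for economic evaluation".

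Table 4, under Implementation evaluation analyses, is the only place that assigns child instruments by age. For children under 7 and then for older ones it reads "Parent reported Paediatric Quality of Life Inventory [9] CYP aged 7–17 years: CHU9D [10". The two groups do not overlap, and no child instrument is listed for age 18.

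The Economic evaluation section names parent EQ-5D-5L, PedsQL and CHU9D without an age split and continues: "These utilities will be included in the estimation of QALYs (quality-adjusted life-years) by calculating the area under the curve".

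**The concern.** These statements cannot all hold. A PedsQL result based on 400 children aged 0 to 18 needs PedsQL at every age, whereas Table 4 stops it at 7. Someone building the surveys from Table 4 would not collect PedsQL from older children, and a missed enrolment measurement cannot be recovered later.

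If Table 4 is followed, there are three consequences:

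- The pre-post PedsQL comparison rests on the under-7 subset and says nothing about older children.
- No child has both instruments at the same survey, so the use of CHU9D that Table 1 describes has no paired data in this cohort to rest on.
- If age at each survey decides the instrument, a child who turns 7 during follow-up changes instrument and loses the pre-post comparison.

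The Economic evaluation adds a wording problem. It counts PedsQL among the utilities, although the sample-size paragraph treats it as a scale score. A scale score needs a conversion before it can enter a QALY.

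**Working it through.** **Inputs from the protocol article.** Intervention cohort 400; difference 4.36 points, compared within children (post versus pre); cohort aged 0 to 18; PedsQL under 7 and CHU9D at 7–17 according to Table 4.

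**Inputs not given, so assumed.** Two-sided alpha 0.05; SD of the change score 15, 20 or 25 points; ages spread evenly over 18 years; no attrition in either scenario, so that the comparison isolates the age split.

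**Formulas** (paired mean change, normal approximation):

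- power = Φ(4.36·√n / SD − 1.960)
- largest SD giving 90% power = 4.36·√n / (1.960 + 1.282)
- n for 90% power = (SD × 3.242 / 4.36)²

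**Step 1: the plan's own claim.** It cannot be reproduced exactly, because SD, alpha and power are not stated for PedsQL. It is plausible at n = 400: 4.36 × 20 / 3.242 = 26.9, so 90% power holds for any SD of change up to 26.9 points (up to 31.1 for 80% power).

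**Step 2: the under-7 subset.** 400 × 7/18 = 155.6, about 156. If age 18 is counted as a full nineteenth year, 400 × 7/19 is about 147.

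**Step 3: children who switch instrument.** Every child enrolled at age 6 is 7 by the 12-month survey. With even ages that is 400/18, about 22 children. If age at survey decides the instrument, about 400 × 6/18 = 133 can have PedsQL at both enrolment and 12 months.

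**Step 4: results.**

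| PedsQL sample | n | Largest SD for 90% power | Power, SD 15 | SD 20 | SD 25 |
|---|---|---|---|---|---|
| All children | 400 | 26.9 | >99% | 99% | 94% |
| Under 7, even over 18 years | 156 | 16.8 | 95% | 78% | 59% |
| Under 7, even over 19 years | 147 | 16.3 | 94% | 75% | 56% |
| Under 7 at both enrolment and 12 months | 133 | 15.5 | 92% | 71% | 52% |

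Worked example, n = 156 and SD 20: 4.36 × 12.49 / 20 = 2.72; 2.72 − 1.96 = 0.76; Φ(0.76) is about 0.78. A noncentral t calculation agrees within about 0.01 for every cell shown.

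**Step 5: number needed.** For 90% power, 125 paired children at SD 15, 222 at SD 20 and 346 at SD 25. The target of 400 covers all three. The illustrative under-7 subset covers only the first.

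**The case against.** The strongest reply is that Table 4 may simply be the error. It summarises data sources by research question, while the section that describes data collection gives PedsQL and CHU9D to the intervention cohort with no age limit, as do the sample-size paragraph and the economic section. If so, the 400-child basis stands and the loss of power disappears. This is fair. It is why the point is an unresolved contradiction and not a demonstrated gap in measurement. A reader might infer from Table 4 that most of the cohort has no PedsQL, or that neither the claim nor the QALYs cover the cohort. The document does not support either as fact. PedsQL and CHU9D together reach ages 0–17 even under Table 4, and Table 1 signals a route from PedsQL to QALYs.

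A second reply is that the power figures rest on assumptions. That also stands. The age mix, SD of change and follow-up rate are all unstated. The cohort section admits infants under 6 months without requiring frequent service use, so the ages may well not be even. No stated PedsQL power is refuted, because none is given.

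A third reply concerns the QALYs. A reader might infer that parent and child values will be pooled into one figure. The economic section does not say so, and separate parent and child QALYs fit its wording. The conversion algorithm is a detail that an article may leave to a fuller plan, so its absence is not counted here. What remains is that PedsQL is called a utility and that, under Table 4, the two child instruments never meet in one child at one survey.

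**Conclusion.** The contradiction is real, and nothing in the document resolves it. Either Table 4 is wrong, or the 4.36-point claim is tied to a sample that will not supply it. If Table 4 governs, the claim covers under-7s only. On the illustrative even-age assumption the sample falls from 400 to about 156, and the largest SD of change compatible with 90% power falls from 26.9 to 16.8 points.

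It would be too strong to conclude that 4.36 points becomes undetectable. With an SD of change of about 15 or less and some 125 paired under-7s, 90% power survives. The restriction of the result to young children holds whatever the SD. The matter concerns a secondary outcome and the cost-utility analysis; the primary outcome, linked health service use, is unaffected. It should be corrected because it changes either what is collected or what the stated claim covers.

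**What to change.** Make Table 1, Table 4, the patient and family reported outcomes section, the sample-size paragraph and the Economic evaluation agree on which ages receive which instrument, including age 18 and children who turn 7 during follow-up. There are two routes:

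- **Collect PedsQL at all ages.** Correct Table 4 so that an age-appropriate form of PedsQL is given to every child at all three surveys. This keeps the 400-child basis and costs at most one short extra questionnaire for older children.
- **Keep the age split.** Restate the 4.36-point claim for the expected number under 7, with its SD of change, alpha and power, and limit its conclusion to that age group. This costs a wording change and probably a less favourable figure.

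In either case, reword the Economic evaluation so that the PedsQL scale score is not called a utility. Base child QALYs on CHU9D utilities or on a stated PedsQL-to-CHU9D conversion, give the ages they cover, and report parent EQ-5D-5L QALYs separately. This part costs only text.
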